### Procedures

#### Recruitment and Consent

Advertisement for this study will take place primarily online (social media) and through partner advocates (Postpartum Support International and Maternal Mental Health Leadership Alliance). Pregnant military-affiliated individuals who reside in the United States are eligible. Interested participants will contact the study coordinator for additional information and initial eligibility screening, including verification of military status.

#### Telephone Interview and Screening

Participants who meet initial inclusion criteria and have completed the consent and baseline questionnaires will be contacted for a telephone interview to assess further eligibility. The interview will contain items of the Structured Clinical Interview for Diagnostic and Statistical Manual of Mental Disorders-5-Clinical Version [42] and the Structured Clinical Interview for Sleep Disorders-Revised [43]. Eligible participants will be randomly assigned to either SB group or TB group. The SB will be shipped to the participants and returned after M6 at no expense to them. TB group participants will be shipped a standard bassinet (HALO BassiNest Swivel Sleeper) to keep. Mother-infant dyads (up to N=342) will be randomly assigned to conditions by using a random number generating program found on a widely used and reputable website [44]. We will perform 1:1 randomization. Variability in the length of bassinet usage may be impacted by size of infant, parental preference, or infant temperament. However, data will be collected through 6 months post partum.

#### Data Collection

For each assessment (Figure 1), all participants will receive an email with a REDCap (research electronic data capture) link for web-based data collection. All web-based survey data will be published in accordance with the CHERRIES (Checklist for Reporting Results of Internet E-Surveys) checklist. To mitigate and minimize the possibility of missing data in the measures, we will program electronic questionnaires to prevent skipping questions. REDCap is a web application and back-end database model designed to support data capture for research studies. REDCap is an open-source tool developed by Vanderbilt University to build and manage web-based forms for data collection. REDCap was developed specifically based on guidance from the Health Insurance Portability and Accountability Act of 1996 security guidelines and contains features such as data encryption. In addition, participants will receive a monthly package containing 2 actigraphs, a baby’s day diary, and a prepaid return envelope.

### Measures and Materials

Table 1 describes the schedule of the study assessments for primary and secondary measures.

**Table 1 table1:** Assessments and timeline.

Measures			Baseline enrollment		1 month PP^a^		2 months PP		3 months PP		4 months PP		5 months PP	6 months PP
**Maternal screening measures**														
	Consent/inclusion/exclusion	✓												
	Demographics	✓												
	SCID^b^ depression module/sleep SCID	✓												
	Infant assessments													
	Actigraphy			✓		✓		✓		✓		✓		✓
	Brief Infant Sleep Questionnaire			✓		✓		✓		✓		✓		✓
	Infant Behavior Questionnaire-Revised			✓		✓		✓		✓		✓		✓
	Baby Cry/Fuss chart			✓		✓		✓		✓		✓		✓
**Maternal assessments (primary)**														
	Sleep diary			✓		✓		✓		✓		✓		✓
	Actigraphy			✓		✓		✓		✓		✓		✓
	Pittsburgh Sleep Quality Index	✓		✓		✓		✓		✓		✓		✓
	Edinburgh Postnatal Depression Scale	✓		✓		✓		✓		✓		✓		✓
	Generalized Anxiety Scale	✓		✓		✓		✓		✓		✓		✓
	Tasso blood collection kit (Epigenetics)	✓												
	Blood samples (inflammation)	✓						✓						✓

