**Methods:**

This study is a 6-month, parallel-arm, randomized controlled trial. Pregnant women (N=342) in the third trimester will be randomized at 1:1 ratio to use a smart bassinet (SB) or a standard commercially available bassinet (HALO BassiNest Swivel Sleeper 3.0; traditional bassinet [TB]) for up to 6 months after delivery. Participants will have their infants sleep in the bassinet, complete monthly web-based questionnaires, and record sleep data with diary and actigraphy for both the participants and their infants for 1 week each postpartum month. Blood samples will also be collected at baseline (late pregnancy) and at 3 months and 6 months post partum to assess immune functioning. The primary outcomes for this study will be postpartum mood (depressive and anxiety symptoms) and infant and maternal sleep. In addition, we are evaluating whether SB has a significant impact on immune functioning—a marker that physiologically connects sleep and mood symptoms.

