Determine whether the use of a smart bassinet (SB) augments infant sleep and improves maternal sleep during the first 6 months post partum compared to the use of a traditional bassinet (TB). (1) Hypothesis 1a: Infants who sleep in SB will have better sleep (ie, diary and Brief Infant Sleep Questionnaire as maternally reported) [40] than those who sleep in TB. Outcomes will include maternally reported sleep duration, awakenings, as well as objectively assessed (actigraphy) wake after sleep onset and sleep onset latency. (2) Hypothesis 1b: Mothers of infants who sleep in SB will have better subjectively reported (ie, diary and Pittsburgh Sleep Quality Index) and objectively assessed (actigraphy) sleep compared to those of infants who sleep in TB. Outcomes will be the same as those for infants.Determine the effect of SB on maternal postpartum depressive and anxiety symptoms and evaluate the model that the association between SB and postpartum depressive symptoms is mediated by both infant and maternal sleep. (1) Hypothesis 2a: Mothers of infants who sleep in SB will have fewer postpartum depressive symptoms over time (ie, Edinburgh Postnatal Depression Scale) compared to those of infants who sleep in TB. (2) Hypothesis 2b: SB improves infant sleep, which then predicts better maternal sleep, and thereby predicts lower maternal depressive symptoms.Compare the trajectory of immune system function from late pregnancy through post partum between participants with and without PMADs and between SB and TB groups. (1) Hypothesis 3a: Peripheral cytokines, immune cells, and stimulated cytokine profiles of women with PMADs assessed in late pregnancy and at 3 and 6 months post partum will indicate greater innate immune activity compared to those of women without PMADs. (2) Hypothesis 3b: Mothers of infants who sleep in SB will exhibit lesser innate immune dysfunction than mothers of infants who sleep in TB.Exploratory aim: Evaluate whether the elevated risk demonstrated by previously identified PMAD epigenetic biomarkers at the TTC9B and HP1BP3 genes can be modified by using an SB. We hypothesize that the elevated risk will be reduced in the SB group compared to that in the TB group.

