#### Primary Maternal Assessments

The Consensus Sleep Diary [50] will collect subjective sleep, while actigraphy will be contemporaneously used to derive objective sleep data. The Pittsburgh Sleep Quality Index [51] will measure habitual sleep quality. The Edinburgh Postnatal Depression Scale [52,53] will be used to assess changes in the depressive symptoms over time. The Generalized Anxiety Disorder Scale-7 items [54] and the Perinatal Anxiety Screening Scale [55] will be used to assess anxiety symptoms over time.

Participants will have their blood drawn (up to 20 mL) at enrollment, 3 months post partum, and 6 months post partum at a Quest Diagnostics laboratory near them (Figure 1). Briefly, blood collection kits with ethylenediaminetetraacetic acid tubes will be mailed to participants with a requisition form and a laboratory directive (from Quest) that provides the Quest Diagnostics Patient Service Center instructions on how to collect and process the study kit. Blood samples will be shipped in a temperature-controlled fashion to the Psychoneuroimmunology in Pregnancy & Postpartum (PIPPI) laboratory at Weill Cornell Medical College for analysis. Measurements of circulating cytokines, stimulated cell assays, and flow cytometry analysis will be conducted to evaluate the role of immune dysregulation.

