#### Mean Differences

Initial analyses will be performed to verify that the random assignment procedure successfully equalized participants between the treatment and control groups on the preintervention variables. Thus, MANOVA will compare these 2 groups on the entire set of preintervention baseline measures. A chi-square test will verify that both groups have the same distribution of infant boys and girls. As participants will be randomized to groups using a random number generator, baseline equivalency of the 2 groups is anticipated.

Six separate mixed 2 (treatment vs control) × 6 (assessment period) MANOVA models will be conducted. Specifically, to assess hypothesis 1a (aim 1), the model (model 1) will be applied to the infant sleep quality outcome measures. To address hypothesis 1b (aim 1), the analysis (model 2) will be applied to maternal postpartum sleep quality outcome measures. To evaluate hypothesis 2a (aim 2), the model (model 3) will be applied to the maternal postpartum depression outcomes. To examine hypothesis 3a (aim 3), the model (model 4) will be estimated on the measures involving peripheral cytokines, immune cells, and stimulated cytokine profiles. To examine hypothesis 3b (aim 3), the model (model 5) will be undertaken on the measures of T-cell dysfunction. Furthermore, to examine the exploratory aim, the model (model 6) will be estimated on the epigenetic biomarkers.

In each of the mixed MANOVA models, several follow-up analyses will be conducted to examine the results. First, a mixed (between-subjects and within-subjects) analysis of variance will be applied on each specific outcome. Second, independent 2-sided *t* tests will assess mean differences between the treatment and control group (at each timepoint) on each outcome. Third, dependent 2-sided *t* tests will permit scrutiny of the temporal change in mean scores between every 2 timepoints on every outcome. Fourth, the longitudinal trajectories across the entire 6-month period for both the treatment and control groups will be graphed using 95% CIs to provide a visual tool to offer insights to understand the effectiveness of the RCT.

Prior to conducting analyses, the normal distribution of all the measures will be inspected. If a variable is evidenced to be nonnormally distributed, then the bootstrapping variant of these statistical techniques instead will be performed to obtain corrected *P* values [84].

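### Immune and epigenetic blood measures are labelled primary in Table 1 but not in the abstract or aims, and hypothesis 3b (innate immunity) is tested on unnamed T-cell measures

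*Protocol article*

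**What the plan says.** **Rank of the measures.** The abstract (Methods) states: "The primary outcomes for this study will be postpartum mood (depressive and anxiety symptoms) and infant and maternal sleep". Immune function comes next, outside that list: "In addition, we are evaluating whether SB has a significant impact on immune functioning". The aims in the Introduction make immune function aim 3 without giving it a rank, and they label the epigenetic aim exploratory.

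The Measures and Materials section introduces Table 1 as the schedule for primary and secondary measures. Its block "Maternal assessments (primary" contains both "Tasso blood collection kit (Epigenetics", ticked at baseline only, and "Blood samples (inflammation", ticked at baseline, month 3 and month 6. The text section on primary maternal assessments also covers the immune work: "Measurements of circulating cytokines, stimulated cell assays, and flow cytometry analysis will be conducted to evaluate the role of immune dysregulation".

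**The test of hypothesis 3b.** The aims state: "Mothers of infants who sleep in SB will exhibit lesser innate immune dysfunction than mothers of infants who sleep in TB". No marker, score or visit is named. The Mean Differences section assigns 3b to model 5, a mixed MANOVA on outcomes described only as T-cell dysfunction. As follow-up to each MANOVA, "a mixed (between-subjects and within-subjects) analysis of variance will be applied on each specific outcome", and t tests then compare the arms on every outcome at every timepoint. These follow-ups are not said to depend on the MANOVA result.

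The section on statistical analyses for immune measurements mentions a combined score of peripheral innate cytokines. It uses the score to compare women who do and do not develop a postpartum mood or anxiety disorder (PMAD), not to compare SB with TB.

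**The concern.** There are two defects, and each makes the other worse.

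First, the document gives the immune measures two ranks and the epigenetic kit two ranks. Someone reporting an immune difference between arms could cite Table 1 and call it primary, or cite the abstract and not.

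Second, hypothesis and model do not match. The hypothesis concerns innate immunity. The model analyses T-cell function, and its outcomes are not listed. Carrying out the plan as written would not test 3b as stated. Because each outcome is also tested separately, an isolated significant marker could be read as support for 3b and, through Table 1, as a primary finding.

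The mood and sleep endpoints are not affected. At stake is the standing and meaning of any claim that SB improves immune function.

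**Working it through.** **1. Rank, place by place**

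| Measure | Abstract, Methods | Aims (Introduction) | Table 1 | Primary Maternal Assessments text |
|---|---|---|---|---|
| Mood, maternal sleep | primary | aims 1 and 2 | primary | included |
| Immune blood work | outside the primary list | aim 3, no rank | primary | included |
| Epigenetic kit | not mentioned | exploratory | primary | not included |

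For the immune measures, the conflict is between the abstract on one side and Table 1 with the assessments text on the other. For the epigenetic kit, it is between the aims and Table 1. The Power section agrees with the abstract: it works from pilot sleep and mood data and gives no immune effect size.

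**2. Hypothesis against model**

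- Hypothesis 3b: innate immune dysfunction, SB versus TB.
- Model 5, assigned to 3b: T-cell dysfunction, SB versus TB, measures not listed.
- Combined innate cytokine score: innate, but PMAD versus no PMAD.

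No planned analysis is at once innate, a comparison of SB with TB, and assigned to 3b.

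**3. Size of the chance-finding risk**

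The article gives no marker count and no familywise error rate, so there is no figure of its own to reproduce. It states P<.05, two-tailed, for the power analyses only. I assume that level for each follow-up test, with no gating and no adjustment.

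Inputs:

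- *T-cell measures.* The flow cytometry section stains stimulated cells for IFN-γ, IL-4, IL-17A, CD25 with FoxP3, and CD45RO, which suggests about 4–5 readouts. I assume 5 to 8.
- *Other readouts.* Four cytokines at three cortisol concentrations give 4 × 3 = 12, and seven cell populations are named in the first flow panel: 12 + 7 = 19. The Mean Differences section assigns these kinds of measure to model 4 (hypothesis 3a). The models there are specified as treatment versus control, so the measures may also be compared by arm.

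For m independent tests, the chance of at least one false positive is 1 − 0.95^m:

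- m = 5: 1 − 0.95^5 = 22.6%
- m = 8: 1 − 0.95^8 = 33.7%
- m = 19: 1 − 0.95^19 = 62.3%

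For equally correlated two-sided z tests at |z| > 1.96:

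| m | independent | ρ = 0.5 | ρ = 0.7 | ρ = 0.8 |
|---|---|---|---|---|
| 5 | 23% | 18% | 15% | 13% |
| 8 | 34% | 25% | 19% | 16% |
| 19 | 62% | 41% | 28% | 22% |

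These figures are for one postpartum visit. Testing at both month 3 and month 6 would raise them. A single pre-named test at .05 has a 5% chance.

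**The case against.** **Table 1 schedules assessments and does not define endpoints.** Its secondary block includes delivery information and an adherence questionnaire, which are not efficacy outcomes, and the abstract is the explicit statement of primary outcomes. This has some force. A reader might infer from Table 1 that the trial has a primary epigenetic endpoint. The documents do not support that, since the kit is collected only at baseline and cannot be a post-randomisation outcome. For the immune measures the point is weaker: the article presents Table 1 as ranking measures, a secondary block was available, and the text repeats the primary label.

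**The aims do not contradict Table 1 on immune measures.** This stands. Aim 3 carries no rank, so the immune conflict rests on the abstract alone.

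**Hypothesis 3b is not without an outcome set.** This stands as well. A reader might conclude that 3b rests on all 19 or more named immune readouts and carries a false-positive chance of 41% or 62%. But model 5 confines the test of 3b to T-cell measures, and most of the 19 belong to model 4. The 19 also count four cytokines at three concentrations as 12, and some cell populations are nested in others. The smaller T-cell range is therefore the one that applies to 3b itself.

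**Multiplicity belongs in the statistical analysis plan.** A reader might infer that the trial has no multiplicity control. That cannot be concluded: each model opens with a MANOVA, and gating or adjustment may be set out in a plan that is not shown. Such a rule would lower the error figures. It would not remove the conflicting labels or the mismatch between innate and T-cell, both of which are printed in the article.

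**Conclusion.** The point holds in two parts that need no assumption: the article ranks the immune and epigenetic measures inconsistently, and it tests an innate-immunity hypothesis on unnamed T-cell measures.

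The size is conditional. With ungated, unadjusted follow-ups at .05, the chance of at least one false SB–TB difference at one visit is about 15%–34% for 5–8 T-cell measures (ρ = 0.7 to independent). It is about 22%–62% if the 19 other readouts are also compared by arm (ρ = 0.8 to independent). The 5% comparator is the level of one test; the article states no familywise rate. The marker counts and correlations are mine.

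This should be corrected, but it does not threaten the mood and sleep conclusions.

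**What to change.** 1. **Table 1 and Primary Maternal Assessments.** Move the inflammation blood samples, and the text describing the immune assays, from primary to secondary. In Table 1, move the epigenetic kit to an exploratory block or mark it so by footnote.
2. **Mean Differences, model 5.** Reconcile it with hypothesis 3b by letting one test decide 3b: the SB–TB difference over months 3 and 6 in the combined peripheral innate cytokine score. The article mentions this score but does not define it, so its components and scoring must be fixed before analysis. If T-cell function is what is meant, reword 3b accordingly and name one T-cell measure instead.
3. **Everything else immune.** Report the T-cell measures and the remaining cytokines and cell subsets as exploratory, with false-discovery-rate adjusted P values.

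The cost is two relabelled rows, a few sentences and a written definition of the score. No new data are needed. The article expects analysis to finish by July 2028, so the change can be made before results are known. The downside is that an effect on a single marker could be reported only as exploratory.

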**Maternal assessments (secondary)**														
	Insomnia Symptom Questionnaire	✓		✓		✓		✓		✓		✓		✓
	Epworth Sleepiness Scale	✓		✓		✓		✓		✓		✓		✓
	Flinders Fatigue Scale	✓		✓		✓		✓		✓		✓		✓
	Treatment expectations	✓						✓						✓
	Social support survey	✓		✓		✓		✓		✓		✓		✓
	Adherence questionnaire							✓						✓
	Delivery information			✓										

^a^PP: post partum.

^b^SCID: Structured Clinical Interview for Diagnostic and Statistical Manual of Mental Disorders-5.

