## Methods

### Study Design

This study is a 2-arm, parallel-group RCT. Participants will be randomized at 1:1 ratio to either SB group or TB group. Outcomes are assessed at 7 timepoints (Figure 1): late pregnancy (P3) and in postpartum months 1-6 (M1-M6).

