#### Primary Infant Assessments

The mother will record infant sleep for 1 week per month in the baby’s day diary [46]. Boxes are filled in daily for 1 week with symbols that correspond to when the infant is asleep, awake, awake and fussy, sucking, or feeding. This measure has been widely used and exhibits desirable reliability and validity [47,48]. The Brief Infant Sleep Questionnaire [40] is used to assess the infant’s sleep during the past week. The Infant Behavior Questionnaire-Revised [49] will be used to allow mothers to report, on a 7-point scale, the frequency with which infants have enacted specific behaviors in common situations during the past week.

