#### Patient Adherence

Various items will be collected to determine patient adherence: (1) self-reported adherence assessed using an adapted survey checklist provided by [name], (2) self-report data on bassinet usage, (3) pictures of bassinet use by participants, and (4) comment boxes to explain nonadherence.

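### The adherence questionnaire is scheduled at months 3 and 6 only, while outcomes are monthly and bassinet use is expected to end at varying times, so week-level use at months 1, 2, 4 and 5 is not assured

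*Protocol article*

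**What the plan says.** All places are in the protocol article.

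- **Outcome schedule.** Study Design places assessments at "late pregnancy (P3) and in postpartum months 1-6 (M1-M6". The abstract's Methods has participants "complete monthly web-based questionnaires, and record sleep data with diary and actigraphy" for one week of each postpartum month. Table 1 agrees: sleep diary, actigraphy, the infant and maternal sleep questionnaires, and the depression and anxiety scales are ticked at all of months 1 to 6.
- **Adherence schedule.** In the secondary maternal block of Table 1, the row "Adherence questionnaire" is ticked at months 3 and 6 and nowhere else.
- **Expected exposure.** Telephone Interview and Screening states: "Variability in the length of bassinet usage may be impacted by size of infant, parental preference, or infant temperament". It continues: "However, data will be collected through 6 months post partum".
- **Other sources of use data.** Besides the survey checklist, Patient Adherence lists "self-report data on bassinet usage, (3) pictures of bassinet use by participants, and (4) comment boxes to explain nonadherence". No visit or frequency is given. The section on additional factors and covariates includes the timing of the move to a crib, with no instrument or visit stated.
- **Infant diary.** Primary Infant Assessments describes it as follows: "Boxes are filled in daily for 1 week with symbols that correspond to when the infant is asleep, awake, awake and fussy, sucking, or feeding".

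**The concern.** Hypotheses 1a to 2b are worded in terms of infants who sleep in the smart bassinet against those who sleep in the traditional one. The protocol itself foresees that some infants will stop sleeping in the assigned bassinet before month 6. Two of the reasons it gives, parental preference and infant temperament, could plausibly be related to infant sleep and to the mother's state.

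If the arms draw together in months 4 to 6, there are two explanations: the smart bassinet no longer helps, or many infants were no longer in it. Separating them needs a record of where the infant slept in the weeks when sleep was measured. The stated schedule guarantees an adherence questionnaire at only two of the six outcome months. The trial is not blinded, so use reconstructed later from memory could also differ by arm or by how well the infant slept.

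**Working it through.** The plan states no figure on this point that could be reproduced. The check is a count followed by a comparison of passages.

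**Step 1: count the months.**
- Postpartum outcome months (Study Design; Table 1): {1, 2, 3, 4, 5, 6}.
- Adherence questionnaire months (Table 1): {3, 6}.
- Difference: {1, 2, 4, 5}, so 6 − 2 = 4 of 6 outcome months have no scheduled adherence questionnaire.

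**Step 2: see whether another stated source covers those four months.**

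| Source | Where | Timing stated? | Tied to the recorded week? |
|---|---|---|---|
| Adherence questionnaire | Table 1 | Months 3 and 6 | Not stated |
| "self-report data on bassinet usage" | Patient Adherence | No | Not stated |
| Photographs and comment boxes | Patient Adherence | No | Not stated |
| Move to a crib | Additional factors and covariates | No | Not stated |
| Infant day diary | Primary Infant Assessments | One week per month | Yes, but the symbols described record the infant's state, not the place of sleep |
| Brief Infant Sleep Questionnaire | Table 1 | Monthly | Covers the past week; its items are not listed, so whether it records sleep place cannot be judged here |

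No row gives a stated measure of sleep place in the recorded week for months 1, 2, 4 and 5. Nor does any row show that such a measure is absent.

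**Step 3: ask how far a crib-move date would go.** If collected, it would classify each of the six months as before or after the move. It would not capture part-time use, nights spent elsewhere, or a move to somewhere other than a crib.

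**Step 4: ask which analyses depend on it.** Models 1 to 3 under Mean Differences compare randomized groups, and the mediation model starts from smart versus traditional bassinet. Neither needs a monthly exposure record to be valid. Explaining a null or fading effect does, and so would any supplementary analysis of months in use.

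**Step 5: ask whether the effect can be sized.** A dilution estimate needs the proportion still in the bassinet each month and the effect under full use. The article gives neither. The pilot d = 0.33 for depression in the Power section is an average over all postpartum timepoints, among women who used one bassinet or the other, and may already include falling use. Multiplying it by an assumed use rate could count the same loss twice.

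**The case against.** A reader might infer that adherence is assessed at months 3 and 6 and at no other time, that the times of leaving the bassinet are unknown, and that four of the six assessments cannot be linked to use. The article does not support this. Patient Adherence names three further sources, and the timing of the crib move is listed as a covariate. Table 1 is also not exhaustive: adverse events are monitored monthly by questionnaire, and the Perinatal Anxiety Screening Scale and the Childhood Trauma Questionnaire are planned, yet none of them has a row. Absence from the table therefore does not prove that data are not collected. The timing of such items is also detail that a journal article commonly leaves to the full protocol. Nor is a recall window given for the adherence questionnaire, so a three-month look-back is only an inference.

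These points stand, and they limit the claim. They do not remove it. Table 1 is presented as the schedule of primary and secondary assessments, and it places its one adherence instrument at two of the six outcome months, in a trial that expects use to end at varying times. That is a stated choice, not merely an omission.

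It is also fair to say that the harm is bounded. The planned comparison is by randomized group, intention-to-treat analyses are foreseen, and the article specifies no per-protocol or dose-response analysis. A reader might still want to put a figure on the lost effect, but any such figure would rest on invented use paths. Dilution would also occur whatever the adherence schedule, and recording use monthly would explain it without recovering it.

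**Conclusion.** The point holds as a weakness in the timing of exposure measurement. The adherence questionnaire misses four of the six outcome months, and the sources that could fill the gap have no stated timing and no stated link to the diary and actigraphy week. Week-level use at months 1, 2, 4 and 5 is therefore not assured; it is not shown to be unrecorded.

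The comparison by assignment is unaffected. What is at risk is the reading of a null or fading effect, particularly in months 4 to 6, and any supplementary exposure analysis. No numerical size beyond the count of 4 in 6 is supported.

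The conclusion assumes that Table 1 shows the adherence questionnaire's schedule correctly and that no monthly instrument already records sleep place for the recorded week. If one does, stating it in Table 1 resolves the point.

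**What to change.** - **Table 1:** add two or three bassinet-use items at each of months 1 to 6, referring to the same week as the diary and actigraphy: number of nights in the assigned bassinet, any other sleep place, and date of last use. Keep the longer adherence questionnaire at months 3 and 6. If such items already exist, give them a row.
- **Reporting:** present use by arm and month beside the outcome trajectories. Label any analysis of months in use as supplementary.
- **Analysis:** keep the comparison by assignment as primary. Do not adjust it for bassinet use or for the timing of the move to a crib, which the article now lists among its covariates. Both arise after randomization and may be affected by arm, so adjustment could bias the comparison.

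**Cost:** a few items in the existing monthly web survey or diary, and a small extra burden on participants. No new visit or staff is needed. Recruitment began in January 2025, so the change is worth making early: use not recorded at the time can later be recovered only by recall.
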